### The Intervention Group

The patients in the treatment group will be prescribed an individually EBCR program at home and in the hospital. The targeted heart rate and walking distance targets will be set individually based on baseline 6MWT. The intensity progression will be evaluated weekly if tolerated. Exercise education and an exercise guidance book will be provided to patients before the program begins. In the hospital, patients do a 45-minute exercise session consisting of a warm-up (5 min), core exercise (30 min) in the form of walking on a treadmill, and cool down (10 min). This exercise is carried out twice a week over 4 weeks in the hospital (a total of 8 sessions) and is directly supervised by a certified cardiac rehab nurse (Table 1).

During exercise at home, subjects will be monitored by a “TEKAD” telemonitoring system. Patients will wear CovWatch that will be connected via the internet to a web-based system (App Rehab Cardio). Prior to the exercise at home, the researcher and the IT team will ensure that the CovWatch is connected to the dashboard App Rehab Cardio to facilitate the real-time monitoring of patients’ vital signs during exercise (see Figure 2). Home exercise will be carried out for 45 minutes, consisting of 5 minutes of warm-up (eg, simple stretching or slow walking), 30 minutes of core exercise walking based on the exercise dose and patient’s ability, and 10 minutes of cooling down. Vital signs, such as pulse, BP, and oxygen saturation, will be monitored via CovWatch and displayed on the dashboard. Home exercises will be prescribed 3 days a week over 4 weeks (12 sessions in total), with a schedule adjusted by the researchers so as not to coincide with the hospital exercise sessions. Patients will be evaluated and receive weekly exercise reminders directly when they perform exercise at the hospital.

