### The Control Group

The CG will be enrolled in a cardiac rehabilitation program in the hospital. Patients in this group also will receive exercise education before starting the program. They will be scheduled for 2 sessions per week or 8 sessions in total to do individual exercise at the hospital under a CR nurse’s supervision. Based on hospital policy, patients are also suggested to exercise at home independently (without monitoring). Hospital exercises consist of a 5-minute warm-up, 30-minute core exercise (walking on a treadmill), and a 10-minute cool-down (Table 1).

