### Measurement

In this study, respondents will be asked to fill out the participant characteristics, including age, sex, BMI, and medical history, which were collected at baseline through direct interviews and medical record reviews. Sociodemographic information, such as marital status, educational level, occupation, insurance ownership, and average monthly income, was also gathered. In addition, participants were asked about their smoking history (categorized as current, former, or never smoked) and any past or current illnesses, diseases, or risk factors. Clinical information was obtained, including the patient’s medical diagnosis, ejection fraction, prescribed therapies, weight and height, as well as the schedule of heart polyclinic control and cardiac rehabilitation, if applicable.

Adherence to the exercise-based cardiac rehabilitation program as the primary outcome will be measured by recording the number of sessions attended by each participant. Based on a previous study [40], adherence will be calculated as the number of attended sessions divided by the total number of prescribed sessions, expressed as a percentage, with a minimum of 80% session completion considered adherent. Attendance during in-hospital exercise sessions will be directly monitored by CR nurses and recorded in the CR attendance form, while home-based exercise attendance for IG will be verified through the web-based dashboard system. Adherence will be monitored by smartwatch logs and dashboard analytics. We will apply this comprehensive approach to ensure accurate measurement of each participant’s adherence to the prescribed rehabilitation program.

Functional capacity will be assessed using the 6MWT to measure the total distance (in meters) during 6 minutes test (6-minute walk distance) [19,37]. In addition, physiological data such as HR, BP, and oxygen saturation will be continuously monitored using the telemonitoring system (see Figure 2), ensuring the safety and accuracy of HBECTR. To provide a more comprehensive assessment of functional improvement, peak oxygen uptake (VO_₂_ peak) or metabolic equivalents will be estimated based on the distance covered in the 6MWT, using established predictive equations [41,42]. These measurements collectively will provide robust data on the participants’ functional performance following the intervention.

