To analyze the effects of HBECTR on patient adherence as the primary outcome and functional capacity as the secondary outcome, there is no formal multiplicity adjustment planned. The data analysis based on normality assumption will be tested using the Shapiro-Wilk test. If the data comply with the normal assumption, we will use the Student *t* test, and vice versa, nonparametric tests will be used if assumptions are violated. In all statistical tests, *P*<.05 (95% CI) will be considered statistically significant. This structured approach will ensure that statistical methods are properly tailored to the data, supporting robust and meaningful interpretation of the results. The statistical analysis plan has been registered within the protocol to the institutional ethics committee board with the approval number KE/FK/0850/EC/2024.

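### A normality pretest leaves the adherence test unfixed and, if attendance is about 80% or more, leads to a rank test on unequal session scales that mostly favours control

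*Protocol article*

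**What the plan says.** Three parts of the protocol article bear on this point.

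- **Outcome.** Under Measurement, "adherence will be calculated as the number of attended sessions divided by the total number of prescribed sessions, expressed as a percentage", and a second, binary form is added: "with a minimum of 80% session completion considered adherent".
- **Denominators.** Under The Control Group: "They will be scheduled for 2 sessions per week or 8 sessions in total". Under The Intervention Group, the hospital part is also 8 sessions and the home part adds "12 sessions in total", so the HBECTR denominator is 8 + 12 = 20.
- **Test.** The last paragraph of Statistical Analysis Planning covers both adherence (primary) and functional capacity (secondary). It states "The data analysis based on normality assumption will be tested using the Shapiro-Wilk test"; a Student t test follows if normality is accepted, and "nonparametric tests will be used if assumptions are violated". Results with P below .05 count as significant. The paragraph before it names paired t tests or ANCOVA for functional capacity and adherence alike, with no pretest. Nothing says which paragraph governs.

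The article gives no expected mean, SD or difference for adherence. The sample size rests on walk distance.

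**The concern.** Two things are at stake.

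First, the data choose the primary test, and two paragraphs give competing instructions for it. A reader cannot tell in advance which P value is the primary one, or whether it refers to mean adherence or to an ordering of ranks.

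Second, the two possible tests do not ask the same question here. The hypothesis is that HBECTR improves adherence. A t test compares mean attended proportion, which has the same expectation in both groups when true attendance is equal, whatever the number of sessions. A rank test asks whether a randomly chosen patient in one group tends to score higher than one in the other. With 9 possible scores in control and 21 in HBECTR, that can differ from one half even when the means are identical. The pretest can therefore move the primary comparison from a test that holds its level to one that does not.

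**Working it through.** **No planned figure to reproduce.** The article states no type I error, power or effect size for adherence, so the check is a simulation under stated assumptions.

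**Inputs from the article:** K = 20 sessions (HBECTR), K = 8 (control), 30 patients per group, two-sided 0.05, and the Shapiro-Wilk rule.

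**Assumptions:** mean attendance m; between-patient correlation ρ, mainly from 0 to 0.3; Mann-Whitney as the fallback; normality checked per group, with failure in either group triggering the fallback.

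**Why ranks mislead.** Take simple binomial attendance with equal true m.
- m = 0.90: P(score = 100%) is 0.9^8 = 0.43 in control and 0.9^20 = 0.12 in HBECTR. Ties at the top rank favour control.
- m = 0.24: P(score = 0) is 0.76^8 = 0.11 in control and 0.76^20 = 0.004 in HBECTR. Ties at the bottom rank count against control.

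**Model.** Patient i has p_i from a beta distribution with mean m and correlation ρ; attended sessions follow Bin(K, p_i); the score is attended/K. There were 2,500 to 5,000 trials per setting, giving a standard error of about 0.3–0.4 points near 5% and up to 1 point for power.

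**Equal true attendance, 30 per group, ρ from 0 to 0.3 (% of trials):**

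| m | Rank test selected | Student t rejects | Planned rule rejects | of which favours control | of which favours HBECTR |
|---|---|---|---|---|---|
| 24% | 95.5–100 | 4.8–5.4 | 6.0–6.9 | 1.2–2.1 | 4.1–5.0 |
| 35% | 68.4–96.5 | 4.9–5.4 | 5.2–6.2 | 1.7–2.3 | 3.3–3.9 |
| 80% | 99.7–100 | 4.8–5.4 | 5.9–6.4 | 4.6–5.4 | 1.1–1.3 |
| 85% | 100 | 4.5–4.7 | 6.8–7.4 | 5.6–6.4 | 0.6–1.2 |
| 90% | 100 | 4.9–5.1 | 8.6–10.5 | 7.2–10.0 | 0.5–1.5 |

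Repeat runs widen these to about 5–8% at 80–85%, 8–10% at 90% and 8–19% at 95%. At 60% the rank test is selected in only 42–89% of trials, and at 50–75% the planned rule rejects in 5–7%. With 27 per group the pattern is the same (90%: 7.9–9.9%). Checking normality on pooled residuals instead still rejects normality in 98–100% of trials at 80% or more, with a level of 6–9%.

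**True HBECTR benefit, power of t minus power of the planned rule (points):**

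| HBECTR v control | Example: t v planned rule | Change over ρ from 0 to 0.3 |
|---|---|---|
| 80 v 70% | 45.9 v 39.0 (ρ = 0.15) | loss 5.8–6.9 |
| 85 v 75% | 52.1 v 42.7 (ρ = 0.15) | loss 7.6–9.4 |
| 90 v 80% | 61.7 v 48.4 (ρ = 0.15) | loss 7.3–13.3 |
| 88 v 80% | 40.2 v 28.5 (ρ = 0.15) | loss 8.4–13.6 |
| 92 v 85% | 49.8 v 32.7 (ρ = 0.1) | loss 17.1 (ρ = 0.1 only) |
| 35 v 24% | 51.0 v 56.5 (ρ = 0.15) | gain 0.6–9.3 |

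Over all beta-binomial runs with high attendance, the loss for a 7–10 point benefit is about 5–18 points. Modelling the groups as mixtures of good and poor attenders gave losses of 19–28.

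**Isolating the cause.** With 8 sessions in both groups and ρ = 0.15, the pretest still sends 100% of trials to the rank test. The level is then 4.8% at 80% and 4.6% at 90%, and no power is lost (80 v 70%: 42.3 against 41.6 for t; 90 v 80%: 60.7 against 57.1). The harm comes from ranking scores on 20-step and 8-step scales; the pretest routes the data there.

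**The case against.** **The size depends on an attendance level that the article does not give.** This stands. A reader might infer that the pretest always works against HBECTR or carries a fixed power cost. The documents do not support that: at mid-range attendance the effect is negligible, and at about 24% false positives favour HBECTR and power rises. The background compliance figures in the Introduction (14–35%, about 24%) are, however, a weak guide, because that text links them to referred patients who never take part. High attendance is plausible, since patients lost before the posttest leave the outcome analysis, but the analysis keeps completers at any adherence level, so it remains an assumption.

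**The pretest is not the cause.** This stands in part. A reader might blame normality pretesting as such, but a Mann-Whitney test fixed in advance would do the same harm. Under this rule the pretest decides whether that test is used.

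**The fallback may be named in the plan lodged with the ethics committee.** This is fair, and leaving it unnamed is not criticised here. The rule itself is stated in the article.

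**ANCOVA is already planned.** It is, but in a paragraph that conflicts with the next one. A reader might infer that walk distance would lose its baseline adjustment; that follows only if the pretest paragraph overrides the ANCOVA paragraph, which the article does not say.

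**It is a nonrandomised pilot, to be interpreted cautiously.** This lowers the severity. It does not remove the point, because P<.05 is still applied to all tests and the result is meant to inform a larger trial.

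**Conclusion.** The concern holds in conditional form and should be fixed, though it is not a fatal flaw. Without any assumption, the primary test of adherence is not fixed, and one permitted route ranks percentages built on 20 and 8 sessions, which does not test a difference in mean adherence.

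The size rests on three assumptions: mean attendance of about 80% or more, beta-binomial spread between patients, and Mann-Whitney as the fallback. On these, the planned rule has a type I error of about 5–8% at 80–85%, 8–10% at 90% and 8–19% at 95%, mostly favouring control, and loses roughly 5–18 points of power for a 7–10 point benefit. A t test stays at about 4–6%.

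The Abstract's sentence that seems to use the t test to check normality is loosely worded. The Methods make the intent clear, so it needs an editorial correction only.

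**What to change.** - **Adherence.** Delete the normality pretest. Fix one primary analysis: the difference in mean attended proportion with a Welch or robust 95% CI, or a quasi-binomial or fractional-logit model with robust standard errors when covariates are included. Keep the rank test only as a labelled sensitivity analysis.
- **Walk distance.** Fix the ANCOVA already named, with a robust or bootstrap 95% CI, in place of the pretest. This keeps an estimate in metres to set against the 30 m difference.
- **Consistency.** Reconcile the last two paragraphs of Statistical Analysis Planning so that each outcome has one named primary test, and correct the Abstract sentence.

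**Cost.** No new data are needed, but this is more than a change of wording. The Results section says that the interventions ended in June 2025 and that the data are being analysed. The change must therefore be dated, disclosed as made at that stage, and accompanied by the result of the test that the published rule would have selected.

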### Safety and Monitoring

Patient safety during exercise is crucial and must be taken into consideration. Clinical supervision and efforts to minimize complications during the exercise program must be implemented to ensure the safety of CR [19]. In this study, the efforts to supervise and maintain patient safety during exercise will involve several aspects related to the program and patients. All patients must obtain a referral from a cardiologist and will undergo an assessment before, during, and after the program. During the recruitment of potential subjects, screening will be conducted, and only patients with a low and moderate risk will be included. We will also educate patients about the signs and symptoms of cardiovascular emergencies, both during exercise at the hospital and home, such as chest pain, irregular heartbeat, weight gain, and shortness of breath. A guidebook will be provided to patients, which details how to perform exercises safely at home and how to use the smartwatch for monitoring. The guidebook also includes the WhatsApp numbers of the researchers and cardiac rehab team and emergency contact details.

Regarding the program, risk stratification screening will be conducted prior to exercise, and patients will be supervised and monitored during exercise. Advances in technology have enabled the remote monitoring of patients, especially when exercise is performed at home or outside the hospital. The safety of remotely delivered CR has been demonstrated by the low long-term rates of reported exercise−related adverse events (AEs), serious adverse events (SAEs), and rehospitalization incidences [48]. Hence, this study will entail the implementation of a telemonitoring system, utilizing the “TEKAD” dashboard for monitoring patients’ vital signs during exercise to ensure the safety of the program (Figure 2).

Prior to participation, all patients will receive comprehensive explanations of the program’s procedures, safety protocols, and communication flow, which will be reinforced again at the start of the intervention. Participants will receive detailed instructions on the prescribed exercise regimen to be performed both at the hospital and at home. They will be guided on the appropriate type, intensity, and duration of exercise and will be encouraged to report any symptoms or discomfort experienced during exercise. If patients experience any adverse symptoms, such as chest pain, shortness of breath, unusual fatigue, or other discomfort, they will be instructed to immediately stop exercising and rest.

During exercise at home, patients will be able to contact the cardiac rehabilitation team via WhatsApp in case of any complaints or concerns. Conversely, if the team detects abnormal changes in vital signs (eg, HR, BP, or oxygen saturation) during remote monitoring, they will proactively contact the patient to inquire about their condition. Then, if necessary, patients will be advised to stop the exercise and take adequate rest.

Furthermore, the risk of AEs and SAEs in EBCR is low. However, it is increased during vigorous intensity exercises relative to rest [49] and intensive exercise training (≥7 times per week) [50]. Therefore, this study will implement the moderate intensity exercise within 5 times per week. Besides, the exercise prescription will be individualized based on the 6MWT baseline, following the CR guideline in Indonesia [19]. All AEs or SAEs during the study will be reported to the cardiologist who will be supervising this program. These also will be documented in the case report form and reported to the ethical board.

### Ethical Considerations

This study protocol adhered to the Declaration of Helsinki and received approval from the institutional review board of the Faculty of Medicine, Public Health, and Nursing, Universitas Gadjah Mada (approval number KE/FK/0850/EC/2024). All participants signed an informed consent form before the study commenced, ensuring their voluntary participation and the protection of their confidentiality throughout the study. The subjects in both groups who will attend on-site rehabilitation sessions at the hospital will receive financial compensation to reimburse transportation costs. This compensation will be provided to support the travel costs incurred during study participation and will not intend to constitute an inducement to participate. The amount and mechanism of reimbursement have been reviewed and approved by the institutional ethics committee.

Emphasizing that the health information of patients is sensitive and the leakage of the information could bring both ethical and economical risks [51], all data obtained will be carefully documented and stored in an encrypted system, and patient confidentiality will be maintained following research ethics standards. Furthermore, the app or dashboard is available only to the researcher team and is password-protected.

This trial was retrospectively registered to the ANZCTR with registry ID: ACTRN12625001400459 (IRRIDDERR1-10.2196/81067). The first enrolment was started at August 14, 2024, while the trial registration was submitted on October 15, 2025 The trial was registered retrospectively due to an administrative and tehnical problem related to the app development.

## Results

The recruitment of the subject started from August 2024. This study is being funded since February 2025. During the submission, we have recruited 63 subjects for both IG and CG. The intervention for both groups finished in June 2025, and the data are being analyzed. It is expected that the data analysis will be finished in November 2025 and that the results will be published in December 2025.

## Discussion

The low adherence of patients to participate in CR programs, particularly after PCI, remains a significant challenge in Indonesia and other countries. Despite class 1 recommendations for CR as part of secondary prevention, CBCR is often underutilized due to various factors, including transportation difficulties, limited availability, and low patient motivation. This study aims to address these challenges by implementing an HBECTR program to enhance patients’ adherence to CR.

This HBECTR intervention protocol offers an innovative approach to CR by leveraging technology to provide continuous monitoring, guidance, and feedback to patients. Previous studies have indicated that home-based cardiac telerehabilitation can be as effective as traditional hospital−based programs in improving functional capacity, adherence, and quality of life [15]. However, there has been limited evidence on home-based cardiac telerehabilitation implementation in Indonesia, particularly in post-PCI patients.

By integrating a telerehabilitation model in HBCR, this study may address several barriers to traditional CR, including geographical challenges and logistical issues. Digital technologies have revolutionized CR, offering flexible and novel approaches to care. The integration of digital health technologies and artificial intelligence in remote CR is transforming traditional paradigms, providing real-time access to health data, and enhancing patient self-management. Mobile and digital CR models, including synchronous or real-time digital interventions, are addressing accessibility barriers and promoting equity in health care delivery [23,27].

Despite the benefit or positive aspect of HBECTR, there are several challenges such as digital literacy, data privacy, and security that must be addressed to ensure the inclusive implementation of CR. Moreover, the shift toward digital CR raises concerns about cost, safety, and potential depersonalization of therapeutic relationships [27].

Furthermore, several potential limitations should be acknowledged in this quasi-experimental study. First, the intervention may yield null or minimal effects, particularly on adherence to cardiac rehabilitation and functional capacity, due to variability in participant engagement, baseline fitness levels, or external barriers such as comorbidities or limited motivation. Second, feasibility challenges are anticipated, including variable access to technology, differences in digital literacy, difficulties in remotely monitoring safety, and potential missing data from nonadherence or technical issues. Using a wearable device (smartwatch) is preferable to most patients; however, it has challenges in its implementation and needs further exploration to gain a deeper understanding of patients’ needs and preferences [52]. Finally, resource limitations may constrain implementation, including limited personnel for supervision, insufficient devices for remote monitoring, costs associated with web-based platforms, and the need for staff training and scheduling coordination.

In addition, this study also has limitations, including its modest sample size, and the short follow-up duration limits its generalizability to the broader population. These are intentional features of a pilot feasibility trial that focuses on testing feasibility, safety, and preliminary efficacy signals rather than providing conclusive evidence of effectiveness [32]. Clinical trials of physical activity and rehabilitation interventions are challenging; therefore, researchers can use pilot and feasibility studies to enhance the rigor of future trials [35].

Despite these challenges, the study provides valuable insights into the practicality and potential impact of HBECTR, informing the design of larger, fully powered trials. Future research is needed to enhance the study in multicenters with multiple outcomes. Longer-term effects, sustainability, and cost-effectiveness should be evaluated in a subsequent definitive trial.
